**Appendix 2, Table 2 Schedule of Procedures, All Arms Long-Term Follow-Up, Month 3 through Year 5**

|                                  |                                                     | Timepoint: months following final CAR T cell infusion |         |         |                   |          |                   |          |                   |          |                   |          |                   |
|----------------------------------|-----------------------------------------------------|-------------------------------------------------------|---------|---------|-------------------|----------|-------------------|----------|-------------------|----------|-------------------|----------|-------------------|
|                                  |                                                     | Month 3                                               | Month 6 | Month 9 | Month 12 (Year 1) | Month 18 | Month 24 (Year 2) | Month 30 | Month 36 (Year 3) | Month 42 | Month 48 (Year 4) | Month 54 | Month 60 (Year 5) |
| Procedure Window →               |                                                     | ± 3 months                                            |         |         |                   |          |                   |          |                   |          |                   |          |                   |
| Medical history    |                                                     |                                                       | X       |         | X                 |          | X                 |          | X                 |          | X                 |          | X                 |
| Physical exam        |                                                     |                                                       | X       |         | X                 |          | X                 |          | X                 |          | X                 |          | X                 |
| CSF                |                                                     | X                                                     | X       | X       | X                 |          |                   |          |                   |          |                   |          |                   |
| Correlative Sciences: PB         | CAR T cell persistence                  |                                                       | X       |         | X                 | X        | X                 | X        | X                 | X        | X                 | X        | X                 |
|                                  | Replication-competent lentivirus (RCL)  | X                                                     | X       |         | X                 |          |                   |          |                   |          |                   |          |                   |
| MRI brain & spine  |                                                     | X                                                     | X       | X       | X                 |          |                   |          |                   |          |                   |          |                   |
| Adverse events       |                                                     | Continuous                                            |         |         |                   |          |                   |          |                   |          |                   |          |                   |

 If performed for clinical indication. May be obtained from local provider or treating oncologist

 Medical events relevant to subject's disease and treatment, inclusive of infectious disease. If relevant, records pertaining to disease response and/or relapse will be collected.

 Testing at all time points must include cell count and cytology. Any additional material obtained for clinical purposes may be sent to CSL for research testing. Disease Evaluations are no longer required if progressive disease was confirmed in a prior evaluation.

 Timepoints only applicable if ongoing T cell persistence in peripheral blood at the end of protocol therapy/discontinuation visit. CAR T cell persistence testing will be discontinued after a negative result.

 MRI of the spine for subjects with previous spinal disease, positive CSF cytology, or cause for clinical concern. Disease Evaluations are no longer required if progressive disease was confirmed in a prior evaluation.

 The following are Delayed Related AEs of interest that must be reported to the Sponsor: development of a new malignancy, or neurologic, rheumatologic, autoimmune, or hematologic disorder

 RCL testing will be discontinued if no positive results during the first year. Further time points may be determined by sponsor after review with FDA if RCL testing is positive at any time during the first year.

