## **7.19 Post-Treatment Long-Term Follow-Up data collection**

Research participants who receive engineered T cells will be required to participate in long-term follow-up (LTFU) per the guidelines set forth by the FDA's Biologic Response Modifiers Advisory Committee that apply to gene transfer studies to capture delayed adverse events related to the use of lentivirally transduced T cells.

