### **7.19.1 Post-treatment long-term follow-up data collection**

For the first 5 years following treatment with CAR T cells, patients will be seen at least yearly. The visit will include an interval medical history and physical exam, specifically eliciting for the development of delayed, related AEs of interest, i.e., malignancy, neurologic disorder, rheumatologic or autoimmune disorder, or hematologic disorder. Unexpected medical problems felt to be related to the CAR T cells will be collected. If subjects are not able to be seen at study site, they may be seen by their primary physician for a physical exam and a blood draw courier kit will be provided to obtain research samples. The physician will be provided with adverse event screening guidelines and will be requested to notify the study team of all new malignancies and unexpected illness felt to be related to the CAR T cells.

Following the first 5 years of LTFU, patients who do not have evidence of persisting gene modified T cells will be contacted yearly by phone for an additional 10 years (for a total of 15

years of LTFU). For those patients who have continued persistence of transferred T cells, they will continue to be seen yearly for LTFU for at least a total of 15 years.

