**Appendix 2, Table 3 Schedule of Procedures, All Arms *Long-Term Follow-up, Years 6 through 15***

| Procedure Window →                                                    | Timepoint: years following final CAR T cell infusion |        |        |        |         |         |         |         |         |         |
|-----------------------------------------------------------------------|------------------------------------------------------|--------|--------|--------|---------|---------|---------|---------|---------|---------|
|                                                                       | Year 6                                               | Year 7 | Year 8 | Year 9 | Year 10 | Year 11 | Year 12 | Year 13 | Year 14 | Year 15 |
|                                                                       | ± 2 months                                           |        |        |        |         |         |         |         |         |         |
| Medical history                                 | X                                                    | X      | X      | X      | X       | X       | X       | X       | X       | X       |
| Physical exam                                   | X                                                    | X      | X      | X      | X       | X       | X       | X       | X       | X       |
| Correlative Sciences: PB CAR T cell persistence | X                                                    | X      | X      | X      | X       | X       | X       | X       | X       | X       |
| Adverse events                                     | Continuous                                           |        |        |        |         |         |         |         |         |         |

- 1 May be obtained from local provider or treating oncologist
- 2 Interim medical history relevant to subject's disease, treatment and status; this information may be obtained by phone, unless subject has evidence of ongoing CAR T cell persistence or RCL, in which case subject must be seen in person
- 3 Timepoints only applicable if ongoing T cell persistence in peripheral blood at the 60-month visit. CAR T cell persistence testing will be discontinued after a negative result

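### Protocol Appendix 2 Table 2 makes the history and physical exam of follow-up years 1 to 5 conditional on clinical indication, contradicting Section 7.19.1, which requires both at least yearly

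*Protocol*

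**What the plan says.** Protocol Section 7.19 makes long-term follow-up mandatory for everyone who receives engineered T cells, in order to capture delayed adverse events. Exclusion criterion 8 in Section 3.2.2 bars anyone unwilling to take part in it.

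Section 7.19.1 sets the frequency: "For the first 5 years following treatment with CAR T cells, patients will be seen at least yearly". It also sets the content: "The visit will include an interval medical history and physical exam, specifically eliciting for the development of delayed, related AEs of interest". Its one relaxation concerns who does the exam. Subjects who cannot reach the study site are covered as follows: "they may be seen by their primary physician for a physical exam".

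Appendix 2 Table 2 covers Month 3 through Year 5. The two relevant rows are labeled "Medical history 1,2" and "Physical exam 1", so both carry footnote 1: "If performed for clinical indication. May be obtained from local provider or treating oncologist". The CSF and MRI rows carry the same footnote.

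Appendix 2 Table 3 covers Years 6 to 15. Its footnote 1 says only "May be obtained from local provider or treating oncologist", with no clinical-indication condition.

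**The concern.** One part of the protocol says the yearly history and exam will be done. Another says they count only if there was a clinical reason to do them. The schedule is not a side document: Section 7 points to Appendix 2 for the required activities, and Sections 7.3 and 7.5 say that history and physical exams are done per the Schedule of Procedures. A site that starts from those sections arrives at footnote 1. A site that starts from Section 7.19.1 arrives at the opposite instruction. No rule says which prevails.

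At stake is how delayed malignancy and delayed neurologic, rheumatologic, autoimmune and hematologic disorders are found after a lentivirally modified product. If the contact at which subjects are asked and examined is optional, those assessed are a self-selected group, and it is hard to say out of how many subjects the delayed events were counted.

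**Working it through.** The plan states no figure to reproduce. The check sets the texts side by side and counts cells.

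**History and exam, years 1 to 5**

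| Item | Section 7.19.1 | Appendix 2 Table 2 |
|---|---|---|
| Who | All treated subjects | Those with a clinical indication |
| How often | At least yearly, so at least 5 visits in 5 years | Months 6, 12, 24, 36, 48, 60 |
| What may be relaxed | Who performs the exam | Whether history and exam are done at all |

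- Cells in the two rows: 2 × 6 = 12.
- Cells carrying footnote 1: 12.
- Unconditional history or exam cells: 12 − 12 = 0, against at least 5 yearly visits under Section 7.19.1.

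**Where the footnote does fit.** Section 7.18.2 makes disease assessment at months 3, 6, 9 and 12 after the final infusion depend on clinical indication. Footnote 1 therefore agrees with the text for CSF and MRI. The conflict is confined to the history and exam rows, which suggests that one footnote was made to serve four rows.

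**What else in Table 2 guarantees a contact after Month 12**

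- Persistence sampling (footnote 4) applies only to subjects with ongoing persistence at the end-of-therapy visit, and it stops after a negative result.
- RCL testing (footnote 7) is scheduled at Months 3, 6 and 12, and it stops if no result in the first year is positive.
- CSF and MRI have no cells after Month 12 and are conditional before then.
- The adverse event row is continuous and does not carry footnote 1. It is a duty to report (footnote 6), not a scheduled contact at which events are elicited.

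A subject with negative persistence and RCL tests therefore has no unconditional scheduled contact in Table 2 after Month 12. The next one is the Year 6 history in Table 3, which may be taken by phone for such a subject.

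**General adverse event capture.** Section 7.9 ends it 28 days after the final infusion, apart from following related events to resolution. Delayed new events therefore depend on the long-term follow-up arrangements.

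**The case against.** The strongest defense is that footnote 1 is a sentence fragment that could be read together with what follows: if the procedure happens to be done clinically, its result may be taken from a local provider. On that reading it concerns data source and makes nothing optional. The reading is possible but strained. The condition stands as its own sentence, and Table 3 expresses the data-source rule without it.

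A second defense is that Section 7.19.1 is specific and unambiguous, that Section 7 calls Appendix 2 a summary, and that Section 9.1 places enrollment at one named hospital, where staff may well follow the text. This limits the likely damage: the harm arises only where the table is applied in place of the text. It does not remove the contradiction, because Sections 7.3 and 7.5 send the reader to the table.

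A third defense is that safety information still arrives by other routes. Adverse event reporting is continuous for all subjects. Under Section 7.19.1, a local physician who sees a subject receives screening guidelines and is asked to report new malignancies and related illness. These points stand, and they rule out any claim that delayed events would go unreported altogether. But the first route is passive, and the second works only if the subject is seen.

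A reader might infer more than the documents support:

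- *That only subjects with symptoms would be assessed.* The footnote refers to clinical indication, which in this population can include routine tumor follow-up.
- *That years 1 to 5 have a weaker schedule than Years 6 to 15 throughout.* This is true of the history row only. Table 3 footnote 5 limits the later exam to subjects with ongoing persistence or RCL.

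**Conclusion.** The contradiction is real and stands in the current text. It is an internal inconsistency, not a deliberate design choice. The firm measure of its size is that 12 of 12 history and exam cells in Table 2 are conditional, where Section 7.19.1 requires at least one visit a year for five years. If the schedule is followed, active eliciting of delayed events becomes selective and the number of subjects assessed becomes unclear. That consequence assumes that the footnote is read as a condition and is applied in place of Section 7.19.1.

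Two further inferences should be resisted. The first is that a planned late-safety rate would be biased. Section 9 specifies no delayed-event rate, and Section 9.5 evaluates overall safety for up to 28 days after the final infusion, so the issue is incomplete ascertainment rather than bias in a defined estimate. The second is a count of subjects missed per year. The protocol does not say how many subjects will still be followed under Table 2 or how many will have clinically indicated visits. Eligibility requires a life expectancy of only 8 weeks or more, and under Section 8.2 both death and transfer to a separate gene-therapy follow-up protocol end participation.

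The point deserves correction because it touches mandatory delayed-safety follow-up and costs almost nothing to settle.

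**What to change.** Reconcile Appendix 2 Table 2 with Section 7.19.1:

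- Detach the Medical history and Physical exam rows from footnote 1 and give them a separate footnote on data source only, in the wording of Table 3 footnote 1: "May be obtained from local provider or treating oncologist".
- Leave footnote 2 on the Medical history row unchanged.
- Keep footnote 1, with its clinical-indication condition, on the CSF and MRI rows, where it agrees with Section 7.18.2.

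The cost is one footnote edit in the next amendment. It adds no visit or procedure beyond what Section 7.19.1 already requires, and the provision for an exam by the primary physician is unaffected.

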**Appendix 2, Table 3 Schedule of Procedures, All Arms *Long-Term Follow-up, Years 6 through 15***

| Procedure Window →                                                    | Timepoint: years following final CAR T cell infusion |        |        |        |         |         |         |         |         |         |
|-----------------------------------------------------------------------|------------------------------------------------------|--------|--------|--------|---------|---------|---------|---------|---------|---------|
|                                                                       | Year 6                                               | Year 7 | Year 8 | Year 9 | Year 10 | Year 11 | Year 12 | Year 13 | Year 14 | Year 15 |
|                                                                       | ± 2 months                                           |        |        |        |         |         |         |         |         |         |
| Medical history                                 | X                                                    | X      | X      | X      | X       | X       | X       | X       | X       | X       |
| Physical exam                                   | X                                                    | X      | X      | X      | X       | X       | X       | X       | X       | X       |
| Correlative Sciences: PB CAR T cell persistence | X                                                    | X      | X      | X      | X       | X       | X       | X       | X       | X       |
| Adverse events                                     | Continuous                                           |        |        |        |         |         |         |         |         |         |

- 1 May be obtained from local provider or treating oncologist
- 2 Interim medical history relevant to subject's disease, treatment and status; this information may be obtained by phone, unless subject has evidence of ongoing CAR T cell persistence or RCL, in which case subject must be seen in person
- 3 Timepoints only applicable if ongoing T cell persistence in peripheral blood at the 60-month visit. CAR T cell persistence testing will be discontinued after a negative result
- 4 The following are Delayed Related AEs of interest that must be reported to the Sponsor: development of a new malignancy, or neurologic, rheumatologic, autoimmune, or hematologic disorder
- 5 Only required for subjects with evidence of ongoing CAR T cell persistence or RCL.

### APPENDIX 3 – PERFORMANCE STATUS SCALES

| Performance Status Criteria                                         |                                                                               |                                             |                                                                                                                     |
|----------------------------------------------------------------------------|-------------------------------------------------------------------------------|---------------------------------------------|---------------------------------------------------------------------------------------------------------------------|
| Karnofsky and Lansky performance scores are intended to be multiples of 10 |                                                                               |                                             |                                                                                                                     |
| Karnofsky
subjects $\geq$ 16 years of age                        |                                                                               | Lansky
subjects < 16 years of age |                                                                                                                     |
| Score                                                               | Description                                                            | Score                                | Description                                                                                                  |
| 100                                                                        | Normal, no complaints, no evidence of disease                                 | 100                                         | Fully active, normal                                                                                                |
| 90                                                                         | Able to carry on normal activity, minor signs or symptoms of disease          | 90                                          | Minor restrictions in physically strenuous activity                                                                 |
| 80                                                                         | Normal activity with effort; some signs or symptoms of disease                | 80                                          | Active, but tires more quickly                                                                                      |
| 70                                                                         | Cares for self, unable to carry on normal activity or do active work          | 70                                          | Both greater restriction of and less time spent in play activity                                                    |
| 60                                                                         | Required occasional assistance, but is able to care for most of his/her needs | 60                                          | Up and around, but minimal active play; keeps busy with quieter activities                                          |
| 50                                                                         | Requires considerable assistance and frequent medical care                    | 50                                          | Gets dressed, but lies around much of the day; no active play, able to participate in all quiet play and activities |
| 40                                                                         | Disabled, requires special care and assistance                                | 40                                          | Mostly in bed, participates in quiet activities                                                                     |
| 30                                                                         | Severely disabled, hospitalization indicated. Death not imminent              | 30                                          | In bed, needs assistance even for quiet play                                                                        |
| 20                                                                         | Very sick, hospitalization indicated. Death not imminent                      | 20                                          | Often sleeping, play entirely limited to very passive activities                                                    |
| 10                                                                         | Moribund, fatal processes progressing rapidly                                 | 10                                          | No play, does not get out of bed                                                                                    |

